### Outcome measures

#### Primary outcome

The primary outcome for this trial is the presence of at least one treated or untreated carious lesion in any permanent tooth measured at the young person-level using the permanent tooth index 'DMFT' (Decayed, Missing and Filled Teeth) where decay is measured as carious lesions extending into dentine - International Caries Detection and Assessment System (ICDAS) levels 4-6 [33], at three years follow-up. The outcome will be measured cross-sectionally at 3 years, and is regardless of the presence or absence of caries in the teeth at baseline.

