##### Sample size

The estimated proportion of UK 12 year olds with caries is 32%, with estimates of 46% for those eligible for FSM and 30% for those not eligible for FSM [4, 40]. Based on a systematic review of interventions for caries prevention to increase the frequency of toothbrushing [41], an absolute reduction in the proportion of young people with caries of 8% might be expected with this intervention. An individually randomised trial powered at 90% (5% two-sided α) to detect a reduction in the proportion of young people with caries from 32% to 24% would require a sample size of 1320. Since this is a cluster trial, this figure needs to be inflated to account for the correlation of the outcomes within schools, as measured by the intraclass correlation coefficient (ICC). Few estimates of a school-level ICC are available for dental data. In a previous study evaluating a behaviour change programme for preventing dental caries in primary schools, an ICC of 0.01 was used, which was estimated using their own unpublished data [42]; a more conservative ICC of 0.02 has been chosen for this trial.

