### Data analysis

All analyses will be conducted on an intention to treat basis, including all randomised young people in the groups to which their year group was allocated irrespective of deviations based on non-compliance, unless otherwise stated. Data from the internal pilot will be used in all analyses.

The primary analysis will compare the proportion of young people with any treated or untreated caries in permanent teeth at 2 and 3 years between the intervention and control groups using a repeated measures binary logistic multilevel model, with the primary time-point of interest at 3 years. The model will control for presence or absence of caries at baseline, year group, time and an interaction between treatment and time as fixed effect covariates. Pupils and school will be included as random effects (to allow for clustering of data within each pupil (over time) and school). Cohen’s kappa coefficient will be used to measure the intra-examiner agreement of presence of carious lesions at ICDAS code 4–6 for 5% of participants who will be examined twice at a particular time point.

A subgroup analysis will be conducted looking at participants with baseline caries by including presence or absence of caries at baseline in an interaction with treatment group in the primary model. The hypothesis is that young people with caries at baseline are more likely to have caries at follow-up than those who do not have caries at baseline.

Secondary analyses will compare self-reported twice-daily brushing frequency at 6 months and 1, 2 and 3 years using a repeated measures binary logistic multilevel model. Continuous measures (Plaque Index Gingival Index of Löe), mean number of bleeding gingival sites per child and CARIES-QC will be analysed using a covariance pattern model. Other secondary outcomes will be analysed using appropriate regression techniques.

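### The baseline-caries subgroup analysis pairs an interaction term with a prognostic hypothesis, and it uses an outcome that pupils with dentine caries at baseline already have

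*Protocol article*

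**What the plan says.** All places are in the protocol article.

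- **Primary outcome** is the "presence of at least one treated or untreated carious lesion in any permanent tooth", scored by DMFT with decay at ICDAS 4-6, so filled and missing teeth count. The section adds: "The outcome will be measured cross-sectionally at 3 years, and is regardless of the presence or absence of caries in the teeth at baseline".
- **Data analysis, primary model**: "The model will control for presence or absence of caries at baseline, year group, time" and a treatment-by-time interaction. Baseline caries is therefore already a main effect.
- **Data analysis, subgroup**: the analysis looks at participants with baseline caries "by including presence or absence of caries at baseline in an interaction with treatment group in the primary model". The rationale given reads: "The hypothesis is that young people with caries at baseline are more likely to have caries at follow-up than those who do not". The comparison is with pupils free of caries at baseline.
- **Secondary outcomes** include the number of permanent teeth with treated or untreated lesions, at ICDAS 1-6 and at 4-6, at 2 and 3 years.
- **Other outcomes** announces an assessment of the impact on young people from deprived areas, using FSM eligibility and IDACI, but gives no model. The baseline-caries analysis is thus the only subgroup analysis with a stated model.

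**The concern.** There are two separate faults.

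**Hypothesis and test do not match.** An interaction asks whether the treatment effect differs between pupils with and without baseline caries. The hypothesis says only that one group will have more caries later and does not mention treatment. Neither a significant nor a null interaction would bear on it.

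**The outcome has a ceiling in the group under study.** A DMFT-based indicator is cumulative: a decayed tooth that is later filled or extracted still counts. A pupil who meets the definition at baseline should meet it again at 2 and 3 years, however many further lesions the intervention prevents.

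At stake is a pre-specified result that is hard to estimate, or that mostly reflects examiner disagreement. A reader could mistake it for evidence about whether the intervention works in pupils who already have caries.

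**Working it through.** The plan gives no figure for the subgroup analysis. Its figure for the main comparison reproduces: for 32% v 24%, 90% power and two-sided 5%, n per arm = [1.960·√(2·0.28·0.72) + 1.2816·√(0.32·0.68 + 0.24·0.76)]² / 0.08² = 660, or 1,320 in total.

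**1. Hypothesis against model.** With logit(p) = a + b·treatment + c·baseline + d·(treatment × baseline), the stated hypothesis is about c, and the added term is d. The primary model already contains c.

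**2. Size of the subgroup.** Inputs: 5,040 pupils (Study setting), 20% attrition and 32% prevalence at age 12 (Sample size). The 32% is a national survey figure, used here as an assumed baseline prevalence at the D4-6MFT threshold.
- Analysed: 0.80 × 5,040 = 4,032.
- Baseline-positive: 0.32 × 4,032 ≈ 1,290, about 645 per arm.
- At 30% to 46% ("with estimates of 46% for those eligible for FSM and 30% for those not eligible for FSM"): about 1,210 to 1,855.

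**3. Without misclassification.** Three-year prevalence in baseline-positive pupils is 100% in both arms. The risk difference is 0 and the odds ratio is not estimable.

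**4. With misclassification.** Assumptions not in the protocol: sensitivity 0.97, specificity 0.99, independent errors across visits, and 25% of new caries prevented. Control incidence is (0.44 − 0.32)/0.68 = 17.6%, taking the Background's 44% at age 15 as an illustrative 3-year prevalence. Intervention incidence is 0.75 × 17.6% = 13.2%.
- Recorded positive at baseline: 0.32·0.97 + 0.68·0.01 = 0.3172, of whom 0.3104/0.3172 = 97.86% are true positives and 2.14% false.
- Recorded positive at 3 years if truly caries-free at baseline: control 0.1765·0.97 + 0.8235·0.01 = 0.179; intervention 0.1324·0.97 + 0.8676·0.01 = 0.137.
- Baseline-positive stratum: control 0.9786·0.97 + 0.0214·0.179 = **95.3%**; intervention 0.9786·0.97 + 0.0214·0.137 = **95.2%**.
- Baseline-negative stratum (0.6732/0.6828 = 98.59% truly negative, 1.41% missed positives): control 0.9859·0.179 + 0.0141·0.97 = 19.1%; intervention 0.9859·0.137 + 0.0141·0.97 = 14.9%.

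The odds ratios are about 0.98 and 0.74. The strata differ only because the outcome cannot register further lesions in pupils who already have one.

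**5. Information in the baseline-positive stratum.** Suppose a share r of its 645 pupils per arm is recorded negative at 3 years (assumed values). SE(log OR) = √[2/(645·r·(1−r))], ignoring clustering.

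| r | Non-events per arm | SE(log OR) |
|---|---|---|
| 1% | 6.5 | 0.56 |
| 2% | 12.9 | 0.40 |
| 5% | 32.3 | 0.26 |
| 10% | 64.5 | 0.19 |

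For comparison, the SE in the baseline-negative stratum (1,371 per arm) is 0.135 if an overall fall from 44% to 36% came entirely from new caries there (17.6% to 5.9%). A higher r gives a smaller SE, but nearly all the non-events it rests on are misclassified pupils.

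**The case against.** **The threshold for baseline caries is not stated.** The Data analysis section gives no ICDAS level, the secondary outcomes use both 1-6 and 4-6, and the SAP, not shown here, may settle it. This stands. If baseline caries meant ICDAS 1-6, pupils with enamel lesions only could still be outcome-negative at 3 years. With D4-6 at 32% and D1-6 at an assumed 50% to 70%, the share able to change would be (50−32)/50 = 36% to (70−32)/70 = 54%. The ceiling would be partial. D4-6MFT remains the natural reading, because the covariate sits in the model for that outcome.

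**The model still yields something useful.** A reader might infer that the analysis can answer no subgroup question. The text does not support that: in baseline-negative pupils, about two-thirds of the sample at 32%, the outcome is new caries and the estimate is interpretable. What fails is the contrast between strata.

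**The hypothesis sentence may only explain the choice of subgroup.** That is possible, and an interaction is the right form for a subgroup test. But the sentence is labelled as the hypothesis, and no effect-modification hypothesis is given.

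**Ignoring baseline status is a deliberate choice for the primary outcome.** It is, and this point does not dispute it there. The choice does not carry over to an analysis meant to look at baseline-positive pupils.

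**Conclusion.** The point holds in a limited form. The mismatch between hypothesis and interaction is plain from the text and depends on no assumption. The ceiling is conditional: if baseline caries is D4-6MFT, about 1,290 analysed pupils (1,210 to 1,855 at 30% to 46% prevalence) have expected 3-year prevalence near 100% in both arms, and the interaction contrast is uninformative. The 95.3% v 95.2% is an illustration. It rests on assumed prevalence, incidence and error rates, but a near-zero contrast follows from the outcome definition itself.

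Two further inferences should not be drawn. The primary comparison is not invalidated by this point, which concerns a secondary analysis. Nor do the documents show that pupils with existing caries are the group of main policy interest: the Discussion and Conclusions frame that interest around deprivation.

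**What to change.** 1. Restate the hypothesis as effect modification: the treatment effect on caries differs between pupils with and without caries at baseline.
2. State the ICDAS threshold and dentition that define baseline caries for the covariate and the subgroup.
3. Test the interaction on an outcome that can change in both strata. The simplest is the number of D4-6MFT teeth at 3 years, already a secondary outcome, adjusted for the baseline count in a count model. The alternative is new D4-6MFT teeth since baseline.
4. If the interaction on the primary outcome is kept, present the baseline-negative estimate as the effect on new caries, and say that the baseline-positive estimate is constrained by the outcome definition.

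This changes analysis wording only and needs no added visits or pupils, provided that baseline caries was recorded by tooth. That is inferred from the baseline dental assessment in the Consent procedure section and is not stated, so it should be confirmed first. The small downside is that the subgroup test is then on a different outcome from the primary one.

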### Health economic assessment

A cost-utility analysis will be conducted. This will estimate the mean differences in costs and quality adjusted life years (QALYs) and report the incremental cost-effectiveness ratio (ICER) for each pathway. The cost-utility analysis will be conducted in line with current recommendations from NICE. In particular, an NHS and Personal Social Services perspective will be taken for costs, and health benefits will be quantified using QALYs. The longer term cost-effectiveness will be modelled to estimate the longer term resource use and HRQoL implications of the intervention.

QALYs will be estimated using the CHU9D [37] reported at baseline and annually thereafter. The CHU9D will be valued using published population tariff values [37, 43], allowing QALYs to be estimated for each arm using the trapezium rule to calculate the area under the curve.NHS resource use will be measured for each participant at baseline and annually up to 36 months. This will include all medication costs (e.g. antibiotics) and visits to dental practices for treatment and health services (e.g. referral to specialists in paediatric dentistry, dental admission for a general anaesthetic) using the parent resource use questionnaire.

### Serious adverse events and adverse events

All participants in the BRIGHT trial will have a dental assessment and complete questionnaires throughout the study period. The intervention participants will receive a CBS about oral health and text message reminders about toothbrushing. Due to the nature of participant involvement, no serious adverse events or adverse events are anticipated that will be unexpected and related.

However, the following procedures will be in place to seek to capture any complications associated with the trial:Young people and parents/carers will be informed in the participant information sheet that they are able to report any concerns or anything out of the ordinary that has happened to them as a result of taking part in BRIGHT to the research team during the course of the study. Contact details are provided.The dental examination case report form will provide space for the dental examiner to record any suspected serious pathologies, safeguarding issues or unexpected and related adverse events or serious adverse events identified at the time of the dental assessment.

The BRIGHT trial team will monitor incoming data in response to these questions.

### Expected events

It is expected that some participants may experience non-serious adverse events such as minor discomfort in their jaw as a result of keeping their mouth open during the dental assessment, similar to that experienced during a check-up at the dentist. It is also possible that some minor bleeding from the gums might occur as a result of checking for the presence of dental plaque during the clinical examination.

It is also expected that there may be unrelated incidents of hospitalisations, illnesses, disabling/incapacitating/life-threatening conditions, other common illnesses and rarely deaths in the study population; we will not seek to record all such events. We only seek to record those that could be related and unexpected.

### Reporting adverse events

Details of any serious adverse events or adverse events reported by the participants will be considered by the principal investigators and research team. Only details of any serious adverse events that are required to be reported to the Research Ethics Committee, i.e. events which are related to taking part in the study and are unexpected, will be recorded using a trial adverse event form. The adverse event reporting period for this trial begins as soon as the participant consents to be in the study and ends at the final data collection point.

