#### Study procedure

##### Randomisation

Allocation will take place within schools by randomising schools 1:1 to one of two regimes:11–12-year-old pupils (year 7 in England and Wales/S1 in Scotland) to receive the intervention and 12–13-year-old pupils (year 8 in England and Wales/S2 in Scotland) to act as the control group, or12–13-year-old pupils (year 8 in England and Wales/S2 in Scotland) to receive the intervention and 11–12-year-old pupils (year 7 in England and Wales/S1 in Scotland) to act as the control group

An allocation sequence, stratified by school using blocks of size two [30], will be generated by an independent statistician. This sequence will be retained by the statistician and will not be accessible to other members of the trial research team. Once a school is ready to be randomised, following collection of their baseline data, the year groups within that school will be randomised by assigning their year 7 and year 8 cohorts (in that order) to the next block in the allocation schedule. The research team and schools will then be informed of which year group has been allocated to receive the BRIGHT intervention and which has been assigned to the control arm. Since the statistician performing the allocation and the teams recruiting the schools are completely separate, and the allocation schedule cannot be known to anyone but the statistician in advance of randomisation, allocation concealment is assured.

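### The adverse event form takes only serious events, so non-serious problems reported by pupils or parents have no stated place to be recorded, although the plan sets out to capture them

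*Protocol article*

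**What the plan says.** Three consecutive sections of the protocol article deal with harms.

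- **Serious adverse events and adverse events.** The expectation is that "no serious adverse events or adverse events are anticipated that will be unexpected and related". Two routes are nevertheless set up to pick up complications. Pupils and parents are told that "they are able to report any concerns or anything out of the ordinary that has happened to them as a result of taking part". The dental CRF has space for suspected serious pathology, safeguarding issues and "unexpected and related adverse events or serious adverse events identified at the time of the dental assessment". The trial team will monitor what comes in.
- **Expected events.** After listing unrelated hospitalisations, illnesses and deaths that may occur, the section says: "We only seek to record those that could be related and unexpected".
- **Reporting adverse events.** Serious and non-serious events "reported by the participants will be considered by the principal investigators and research team". The recording rule for the trial's own adverse event form follows: "Only details of any serious adverse events that are required to be reported to the Research Ethics Committee" are entered there, and the section explains that this means those judged both unexpected and related to participation.

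On who knows the allocation, the Randomisation section states: "The research team and schools will then be informed of which year group has been allocated to receive the BRIGHT intervention". The Blinding section keeps the dental examiner blind where possible and has pupils asked not to talk about the intervention with the dental team.

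**The concern.** The threshold for telling the ethics committee about an event is also being used as the threshold for writing it on the adverse event form. The first safety section treats non-serious related events as worth capturing. The reporting section has them considered but, if they came from a pupil or parent, names no form for them.

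This matters because any harm from a single lesson and twice-daily texts would most plausibly be non-serious. The article says a positive result would support embedding the intervention in school curricula. A harms paragraph showing few or no form entries could then be read as reassurance, when the rule excludes the kind of event most likely to occur.

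**Working it through.** No arithmetic applies: the article states no event rate, harms endpoint or harms comparison. The check compares the texts and then follows a non-serious event along each route.

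**Step 1: scope by section**

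| Section | Seriousness | Relatedness and expectedness | Instrument |
|---|---|---|---|
| Serious adverse events and adverse events: examiner route | serious or not | related and unexpected | dental CRF |
| Same section: pupil or parent route | no limit | reporter attributes it to taking part | none named |
| Expected events | no limit in the sentence itself | could be related and unexpected | none named |
| Reporting adverse events | serious only | are related and unexpected | trial adverse event form |

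Two things change in the last row: non-serious events drop out, and possible relatedness becomes established relatedness. The filters on relatedness and expectedness are not new there, since the earlier sections already apply them.

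**Step 2: a non-serious event found at an examination.** The examiner can write it on the dental CRF. The Data collection section has all CRFs scanned into the trial database. The event is kept, and it is noted by someone blinded where possible before any team review. Nothing is lost here.

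**Step 3: a non-serious problem with the texts or the lesson.** The examiner route is weak for three reasons.

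- It covers only what comes to light at an examination. Under Secondary outcomes, clinical measures are taken at baseline and at the end of years 2 and 3. Under Randomisation, baseline data precede allocation. So the route first operates for intervention effects at the year 2 visit.
- Pupils are asked not to raise the intervention with the dental team.
- An examiner who does not know the arm is poorly placed to judge whether an event is related to the intervention.

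The remaining route is a report by the pupil or parent to the research team. The report is considered by the principal investigators and the research team, the latter having been told the allocation. If the event is not serious, the reporting section gives it no form.

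**Result.** The gap is specific: non-serious events that are, or could be, related and unexpected, and that reach the trial through a pupil or parent rather than an examination.

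**The case against.** The strongest defence is that the CRF captures events and the adverse event form serves ethics-committee reporting, so two instruments with two purposes need not share a scope. This stands for events found at examination. It does not help with pupil and parent reports, which have no instrument other than the one limited to serious events.

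Other points on that side:

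- In the Expected events sentence, the events referred to are those in the preceding list of mostly serious, unrelated incidents. This stands: the sentence is not a free-standing promise to record every minor event, and it carries little weight here. The conflict rests on the other two sections.
- Relatedness is to taking part in the study, and both arms have examinations and questionnaires. This also stands. Control pupils' events can qualify, and the article does not show that everyone considering a report knows that pupil's arm.
- Pupils can stop the texts, quality of life and attendance are collected at years 1 to 3, and there is a process evaluation. These give indirect information but are not a record of harms.
- The article condenses a fuller protocol. That answers what is left out, such as who adjudicates events. It does not answer a stated rule that begins by restricting recording to serious events.

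A reader might infer that an allocation-aware team filters events before anything at all is written down. The documents do not support this, because the examiner's CRF entries come first. A reader might also infer that harms cannot be reported or compared at all. That goes too far: serious related events and CRF entries can both be tabulated by arm. Nor is it useful to turn a zero count into an upper bound on a harm rate, since the article never proposes one.

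**Conclusion.** The inconsistency holds in a limited form. The plan seeks non-serious unexpected and related events, then provides the adverse event form only for serious ones. Those reported by pupils or parents are left without a stated record. The trial therefore cannot reliably report non-serious harms, and few or no form entries would not be evidence that there were none.

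The size of the loss cannot be calculated from the article. The primary outcome and its analysis are untouched, the trial is low risk, and harms are not a listed outcome. The point is worth correcting because the change is cheap and the results are meant to guide wider use.

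Two assumptions underlie this: that no further log of participant reports exists in the full protocol, and that plausible harms of texts and a lesson are mostly non-serious. The second is a judgement, not a figure from the documents.

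**What to change.** - Reconcile the three safety sections to one recording scope.
- Record every event reported by a participant or parent, or noted on the dental CRF, that could be related and unexpected, whether serious or not. Note its seriousness and its source.
- Keep the existing ethics-committee threshold, but only to decide what is reported to the committee.
- Report counts descriptively by arm, and state that spontaneous reporting in a trial where pupils know their group limits the comparison. Recording more events does not remove that limitation.

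Cost: a wording change in the safety sections, a little extra data entry and one descriptive table. Examinations, sample size and ethics-committee reporting stay as they are.
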